### Delivery and Assessment of IPTp intervention

The primary assessment of the IPTp intervention will take place at delivery.

The specific tasks to be completed by the field study team at the delivery visit are as follows:

Baby:

- Record pregnancy outcome (i.e. live birth, stillbirth, abortion)
- Record birth weight
- Collect a heel prick blood sample (200 µl)
  - Prepare thin and thick blood smears
  - Archive a portion of the blood sample for laboratory analyses
  - Measure Hb using Hemacue
- Collect a cord blood sample (approximately 10 ml)
  - Cord haemoglobin concentration
  - Archive a portion of the blood sample for laboratory analyses

Mother

- Interview and record
  - history of bednet use since previous visit
  - history of malaria treatment since previous visit
- Collect maternal peripheral blood (10 ml)
  - Prepare thin and thick blood smears
  - Measure Hb using Hemacue
  - Archive a portion of the blood sample for laboratory analyses
- Collect placental blood films and placental biopsies
- Collect a per-nasal swab

Check the health records booklet for recent health centre visits and record applicable information.

Mothers that deliver at home will be asked to visit Modilon Hospital or a participating health center within no more than a week. In these cases the following tasks will be performed:

Baby:

- Record day of birth
- Record pregnancy outcome (i.e. live birth, stillbirth, abortion)
- Record weight
- Collect a heel prick blood sample (200 µl)
  - Prepare thin and thick blood smears
  - Archive a portion of the blood sample for laboratory analyses
  - Measure Hb using Hemacue

Mother

- Interview and record
  - history of bednet use since previous visit
  - history of malaria treatment since previous visit
- Collect maternal peripheral blood (10 ml)
  - Prepare thin and thick blood smears
  - Measure Hb using Hemacue
  - Archive a portion of the blood sample for laboratory analyses

Check the health records booklet for recent health centre visits and record applicable information.

Before discharge, the field study team will schedule a 6 week post partum visit with the woman and her baby.

### Long-term follow-up following intervention

1. Post partum visit (6 weeks)

This visit will take place concurrent with Health Centre EPI clinics. A week before the scheduled date for the visit, village reporters will visit participating women and their babies, and explain the importance of attending the assessment visit and remind them of time and location of the clinic.

The specific tasks to be completed by the field study team during the Follow-up Visits are as follows:

Child:

- Take health indicators
  - Weight
- Collect heel prick blood sample (approximately 200-250 μl)
  - Prepare thin and thick blood smears
  - Archive a portion of the blood sample for laboratory analyses

Mother of child:

- Interview mother and record
  - history of bed net use since previous visit
  - history of malaria treatment for mother or child since previous visit
- Check the child’s health records booklet for recent health centre visits and record applicable information
- Record maternal weight

Data and responses will be recorded at the time the measurements and interview are conducted on the Follow-up CRF. The participant’s health records booklet will be checked to see if any visits to a health centre have been documented. If the participant has any record of a visit, the field study team will record the date of the most recent visit and any medication the participant received on the CRF.

Women who fail to attend this Visit will be followed-up at their homes by the study team. If found the study team will conduct examination and blood collections at the family’s home.

1. 3 month post partum follow up, selected women

We enrol 250 consecutive participating women into a sub-study of effects of pregnancy on P vivax immunity. Women will attend on one further occasion, 3 months post partum. Tasks to be completed at this visit include:

- Interview mother and record
  - history of bed net use since previous visit
  - history of malaria treatment for mother or child since previous visit
- Check the child’s health records booklet for recent health centre visits and record applicable information
- Record maternal weight
- Collect 10 ml venous sample from mother

1. Final Evaluation Visit (infants only, 12 months of age)

The final assessment of the IPTp intervention will take place at 12 months of age, concurrent with normal EPI clinics. A week before the scheduled date for the visit, village reporters will visit the parents of participating children, explain the importance of attending the assessment visit and remind them of time and location of the next clinic.

The specific tasks to be completed by the field study team during the Final Evaluation Visit are as follows:

Child:

- Take health indicators
  - Weight
  - Measure spleen size
- Collect a finger prick blood sample.
  - Prepare thin and thick blood smears
  - Obtain haemoglobin concentration
  - Archive a portion of the blood sample for laboratory analyses
- Determine if child is suffering from symptomatic malaria or moderate-to-severe anaemia (Hb < 8.0 g/dl)

Mother of child:

- Interview mother and record
  - history of child’s bednet use since previous visit
- Check the child’s health records booklet for recent health centre visits and record applicable information
- Record maternal weight

Data and responses of the participant will be recorded at the time the measurements and interview are conducted on the Final Evaluation CRF.

### Passive Surveillance

1. Health Centre Readiness and Participation

All study villages are situated within areas serviced by the Catholic Health Services through their health centres in Alexishafen and Mugil (Madang North Coast), by Modilon Hospital and nearby Health Centres (Town, Jumba and Sisiak Clinics) (Madang Town) and Yagaum Health Centre (Lutheran Health Services). The health centres outside Madang Town have both in-patient and out-patient facilities and are staffed with a health extension officer and several nurses and community health workers. The health centre staff routinely assess pregnant women for malaria and other intercurrent illnesses. Tertiary referral services are provided by Madang Provincial Hospital

As at all other PNG health centres attendance and admittance log books are kept. Each health centre in the province has a HF radio and radio communication protocols are established for reporting all severe health problems that require further medical support. This radio serves as a communication to the referral hospital in Madang.

The primary investigator and the field study team will meet with the health centre staff prior to initiation of the study to explain the study’s objectives and conduct and review the involvement of the health centres in the study. The field study team will coordinate with the health centre nursing staff for setting up both joint study ANC clinics and a morbidity surveillance system

For the purpose of morbidity surveillance, the PNGIMR maintains a study clinic within the larger health centres and in the Hospital during all out patient clinic hours. The study clinics are staffed with (at least) 1 nursing officer and rural laboratory assistant trained in diagnostic malarial microscopy. Participants will be encouraged to preferably or exclusively visit the participating health centres.

The health centre staff will be requested to screen pregnant women who are attending ANC or outpatient clinics in order to determine if they are study participants. Screening can be accomplished by checking for study symbol and ID numbers on the woman’s Helt Buk (Health Book) or by referring to the list of study participants that will be kept at the study clinics. In addition, women who are participating in the study will be requested to aid the health centres and study team by alerting their health care providers that they are study participants when independently seeking care at one of the participating health centres. After initial diagnosis health centre staff will refer study participants to the IMR morbidity surveillance staff for further clinical investigations and data collections.

1. Diagnosis & Treatment

All participants identified by health centre staff will be referred to the health centre based study nurse. The study nurse will take a medical history and fill in the Health Centre Surveillance form. In the case of participants diagnosed with presumptive malaria, s/he will take a finger prick blood sample to make blood smears, measure haemoglobin and confirm the presumptive diagnosis using on site with a rapid diagnostic test (RDT) or diagnostic microscopy.

Upon confirmation of diagnosis of malaria illness, the participant will be treated by the study nurse with antimalarials. All symptomatic episodes will be treated with the rescue medication (i.e. 3 day course of Coartem). In the case of a haemoglobin < 6.0 g/dl study staff will treat the woman according to PNG national guidelines with a full course of antimalarials, albendazole for hookworm control and iron infusion.

For women with negative RDT/bloodslide and/or Hb ≥6.0 g/dl the health centre staff will be advised to refine the diagnosis for other febrile illnesses and treat accordingly. All women with a diagnosis other than malaria and anaemia will be treated by the health centre /hospital staff.

The study surveillance will only be maintained during official outpatient clinic hours. For women presenting after hours, the health centre staff will be taught how to fill in a simplified After-Hours Surveillance Form, take blood slides, finger prick blood samples and conduct malaria RDTs. The health centre staff will be encouraged to only treat women with antimalarials if the RDT result is positive. The following morning the study surveillance staff will collect blood samples and blood slides from the health centre staff and review forms.

INTERACTIONS WITH AID POSTS Workers at local aid posts will be instructed to refer study women to the nearest health centre for diagnosis and treatment.

1. Health Centre Surveillance Records

The PNGIMR field study team will coordinate with the health centres for the collection and, if necessary, abstraction of specific health information on study participants. Data from the Health Centre Surveillance Forms also are entered into a Health Centre Surveillance Database at regular intervals and maintained by the PNGIMR.

1. Health Records Booklets

All pregnant mothers attending ANC clinics are required to purchase and carry a health records booklet when seeking medical care at health centres. This health records booklet provides information as to the pregnancy as well as illnesses and treatments an individual has had during pregnancy. Additionally, the health records booklets for participants in IMR research studies are marked with a brightly colored sticker.

At enrolment we will thus provide a standard health booklet to each study participant, if she does not have one, free of charge. At delivery of the newborn, we will also provide the mother with a health booklet for her baby free of charge. Each of the health records booklets will be marked with a brightly coloured sticker denoting participation in this study and their study ID number. The sticker number alerts health care providers at the health centres that the individual is participating in the IPTp study, while the ID number allows easy identification of the participant by the surveillance staff.

The field study team will review each participant’s health records booklet at the regular scheduled study visits, record all health care visits on the respective forms.

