**Second line treatment**

Women who are found by passive case detection to be infected with malaria will receive a treatment course of Coartem. Coartem has been adopted as the first line treatment for uncomplicated malaria in all age groups (including pregnant women in 2nd and 3rd trimester) in PNG.

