The study team Physician or a trained study team Nursing Officer will assess the woman for sign of chronic illness, symptomatic severe anaemia or permanent disabilities that would preclude her participation into the study. (See 5.2 for list of exclusion criteria). If a woman is excluded on health grounds, she will be referred to nearest health facility for treatment.

Every enrolled woman’s health (record) booklet (already owned, or provided at enrolment) will be clearly marked with a study identifier and study ID number. At any study contact, the study team will record all medically relevant data collected during their examination into the health booklet.

Digital photographs will be taken of participating women at enrolment, and a printed version will be kept in a secure file, for tracking of pregnant women who fail to attend appointments, and to ensure accurate identification of women if required

Following assessment the woman will receive the 1st IPTp treatment dose. The drugs will be dispensed in pre-randomised and pre-numbered Ziploc bags that contain all drugs for initial treatment. The first dose (SP and AZ or SP and chloroquine) will be dispensed directly by the study staff. Pack number, date and time of administration will be recorded on the enrolment forms. The tablets will be administered with water. The woman will then be instructed how to take subsequent AZ or chloroquine doses at home. The woman’s treatment allocation will be noted using randomly-generated codes. Treatment allocation will not be revealed to laboratory staff, and will be kept concealed to the maximum extent possible from other study staff (see 6.3.3.). Senior study investigators will be aware of treatment allocation; hence the study will be single blinded.

A thorough physical examination (including axillary temperature, measurement of Hb etc. will only be conducted on enrolled women who spontaneously report as ill to either the study team or the health centre staff. Women with a presumptive diagnosis of malaria will be tested on the spot for malaria infection using a rapid diagnostic test (RDT). If they have a positive RDT they will be treated with a full course of Coartem and their randomised IPTp treatment (drug or placebo) will be delayed for at least 4 weeks. For all women reported sick, detailed symptomatology, results of RDT and treatments given will be recorded on the ‘Morbidity Surveillance Form’.

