At the end of the enrolment visit the study team will schedule the next treatment visit with the woman. Participants will be instructed to seek medical attention immediately if they have any sign or symptoms of illness or any other condition that they deem as a threat to their well-being following the treatment. They will also be encouraged to seek medical care if they note any symptoms of malaria, fever, or illness, and to report any antimalarial treatments received or used.

1. 2nd Treatment Visit

During the 2nd treatment visit the PNGIMR study team will conduct the following tasks:

Woman:

- Interview and record
  - history of bednet use in two weeks prior
  - history of malaria treatment in two weeks prior
- Take growth measurements
  - Maternal weight
  - Fundal height
- Collect 250 µl finger prick blood sample
  - Prepare thin and thick blood smears
  - Archive a portion of the blood sample for laboratory analyses
- Check the woman’s health records booklet for recent health centre visits and record applicable information
- Measure maternal blood pressure and check for oedema. If elevated blood pressure or oedema present, women will be tested for proteinuria. Presence of all three will be considered clinical evidence of pre-eclampsia, and women will be referred for obstetric care through Modilon Hospital.
- If possible, perform second ultrasound examination for fetal growth monitoring.

Data and responses of the participant will be recorded on the 2nd Treatment Visit CRF at the time the measurements and interview are conducted. As at enrolment a thorough physical examination (including axillary temperature, measurement of Hb, etc.) will only be conducted on enrolled women who spontaneously report as ill to either the study team or the health centre staff conducting the clinic. Women diagnosed with presumptive malaria will be tested on the spot for malaria infections using a rapid diagnostic test (RDT). If the RDT is positive, they will be treated with a full course of Coartem instead of the scheduled treatment. For all women reported sick, detailed symptomatology, result of RDT and treatments given will be recorded on the ‘Morbidity Surveillance Form’.

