Data and responses of the participant will be recorded on the Final Treatment Visit CRF at the time the measurements and interview are conducted. As at enrolment a thorough physical examination (including axillary temperature, measurement of Hb, etc.) will only be conducted on enrolled women who spontaneously report as ill to either the study team or the health centre staff conducting the clinic. Women diagnosed with presumptive malaria will be tested on the spot for malaria infections using a rapid diagnostic test (RDT). If the RDT is positive, they will be treated according to PNG standard treatment guidelines with a full course of Coartem instead of the scheduled treatment. For all women reported sick, detailed symptomatology, result of RDT and treatments given will be recorded on the ‘Morbidity Surveillance Form’.

Following the collection of data and blood sample the woman will receive the Final IPTp treatment dose (if she is allocated to the SP and azithro arm of the study, or matching SP and Az placebo). Administration will be as for the second treatment dose.

At the end of the visit the field study team will remind the woman of the importance of delivering in the Health Centre or Hospital. Women who fail to attend the study ANC clinic will be contacted by the village reporters and encouraged to present at their local health centre to receive the missed treatment.

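### The passive-surveillance rule gives Coartem for every confirmed symptomatic malaria episode, which is wider than the protocol's only stated basis for the drug: uncomplicated malaria, with the 2nd and 3rd trimester named

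*Combined protocol and SAP*

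**What the plan says.** The stated basis is in the Background, under Second line treatment: "Coartem has been adopted as the first line treatment for uncomplicated malaria in all age groups (including pregnant women in 2nd and 3rd trimester". The sentence just before it has no such limit: "Women who are found by passive case detection to be infected with malaria will receive a treatment course of Coartem".

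The operative instruction is in section 6.1.7, Diagnosis & Treatment. It first places the woman with the study nurse: "Upon confirmation of diagnosis of malaria illness, the participant will be treated by the study nurse with antimalarials". It then fixes the drug: "All symptomatic episodes will be treated with the rescue medication (i.e. 3 day course of Coartem". One separate instruction follows: "In the case of a haemoglobin < 6.0 g/dl study staff will treat the woman according to PNG national guidelines".

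Section 6.1.4 has three further instructions, one per treatment visit:
- Enrolment and first treatment: "If they have a positive RDT they will be treated with a full course of Coartem".
- Second treatment: "If the RDT is positive, they will be treated with a full course of Coartem instead of the scheduled treatment".
- Third treatment: "they will be treated according to PNG standard treatment guidelines with a full course of Coartem instead of the scheduled treatment".

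Sections 6.1, 6.1.3 and 6.1.4 allow women at ≤13 weeks to be enrolled and defer only their IPTp until 14 weeks. The Study Design section runs passive case detection for the whole study and applies it to every participating woman. Appendix II separates uncomplicated malaria, which has no severe signs, from severe malaria, which is marked by impaired consciousness, respiratory distress or Hb <6 g/dl.

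**The concern.** The drug rule staff are told to follow covers more women than the reason given for it. Two groups fall in the gap: participants still at ≤13 weeks, and participants whose malaria shows impaired consciousness or respiratory distress. The protocol provides for clinical assessment of ill women, but 6.1.7 does not say what follows when that assessment places a woman in either group. Staff would have to give the course outside its stated basis, or decide for themselves that general referral text overrides an instruction worded for all episodes. What is at stake is clarity of care for a small number of ill pregnant participants.

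**Working it through.** No arithmetic beyond counting applies, so the check sets the texts side by side.

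**Step 1. The Coartem instructions.**

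| Place | Trigger | Severity limit | Clearly reaches women at ≤13 weeks |
|---|---|---|---|
| Background, Second line treatment (first sentence) | Infection found by passive case detection | None | Yes |
| 6.1.7 | Any confirmed symptomatic episode | None; separate text for Hb <6.0 g/dl | Yes |
| 6.1.4, enrolment and first treatment | Positive RDT | None | Not counted: built around the first treatment |
| 6.1.4, second treatment | Positive RDT | None | No: later visit |
| 6.1.4, third treatment | Positive RDT, tied to national guidelines | None | No: later visit |

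So 0 of 5 carry a severity limit, and 1 of 5 mentions national guidelines but still names Coartem. The gestation question rests on 2 of the 5. One of those two is background text, which leaves 6.1.7 as the only procedural instruction on that limb.

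**Step 2. Gestation.** A woman first seen at ≤13 weeks is enrolled (6.1.3). Passive case detection covers every participating woman (Study Design). The 6.1.7 rule has no gestation condition. It therefore applies to her from enrolment until 14 weeks, that is, for 14 minus her gestation in weeks at enrolment.

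The group is narrow and not cleanly defined. Study Design describes enrolment at 14 to 26 weeks, 6.1.3 keeps first-trimester women in a pre-screening database, and 6.1 assigns the study number at first treatment, so some may not be recognised at surveillance. On the other side, 6.1.7 also uses a participant list, self-identification, and a marked health booklet given at enrolment.

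**Step 3. Severity.** Section 11.1.1 defines a symptomatic infection as parasites on smear and/or a positive RDT, plus fever or recent fever history. There is no upper severity limit, so a severe case is still a symptomatic episode. Appendix II lists 3 severe criteria. Section 6.1.7 gives one of them, Hb <6 g/dl, its own text, and 9.3.2 refers such cases when they are symptomatic. That leaves 3 − 1 = 2 criteria (impaired consciousness and respiratory distress) with no instruction of their own. Section 6.1.7 hands over to health centre or hospital staff only women whose diagnosis is something other than malaria or anaemia, so confirmed malaria of any severity stays with the study nurse.

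**Step 4. Frequency.** None can be computed. The documents give no share enrolled at ≤13 weeks, no first-trimester malaria incidence and no severe-malaria rate.

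**The case against.** The strongest reply is that severe illness is already provided for. Section 9.1 classes serious or life-threatening events as grade 4 and names coma, seizures and altered behaviour. Section 9.2 makes life-threatening events and hospitalisations SAEs. Section 9.3.3 promises best available practice and transport to Modilon Hospital. Section 7.2 refers severe illness found at antenatal visits for appropriate treatment, the Field Study Team section makes physicians responsible for clinical care, and 6.1.7 describes radio contact with the referral hospital. Field detail is also deferred to SOPs that are not in the documents, so a gap in practice is not shown.

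Much of this stands. A reader might infer that a woman with impaired consciousness is left with a nurse and a three-day course. The documents as a whole do not support that reading. Section 7.2 also covers severe illness at the three visits in 6.1.4, so a cross-reference is enough there. But none of this text qualifies the named-drug rule. Section 7.2 sends women to the health centre, which is where the 6.1.7 rule operates, and the adverse-event text does not mention severe malaria or another antimalarial.

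The second reply is that the Background names the 2nd and 3rd trimester without expressly excluding the 1st, and that nothing in the protocol calls Coartem unsuitable before 14 weeks. This also stands. A reader might infer a first-trimester hazard, but the documents do not establish one. The point is only that the instruction is wider than its stated basis. What national guidelines say for ≤13 weeks is not in the documents, so it cannot be shown that treatment would change.

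**Conclusion.** The point holds as a mismatch in scope, centred on 6.1.7 and echoed in one Background sentence. It is minor. It rests on reading the 6.1.7 instruction literally, on women at ≤13 weeks counting as participants once enrolled, and on taking the Background sentence as the protocol's basis for Coartem.

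A reader might also infer that the trial's results are at risk. They are not: the rescue rule is the same in both arms, and the low-birth-weight endpoint, the randomised comparison and SAE capture are unaffected. No view is taken on which drug is right for either group.

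**What to change.** In 6.1.7, and to match in the Background under Second line treatment, state that:
- Coartem is for confirmed uncomplicated malaria at ≥14 weeks, using the best available gestation estimate, with confirmation by RDT or microscopy as now.
- Confirmed malaria at ≤13 weeks is treated under PNG national guidelines.
- An episode with impaired consciousness or respiratory distress is managed as severe malaria under PNG national guidelines, with referral to in-patient care instead of the Coartem course.
- Hb <6 g/dl without either of those signs stays under the existing text in 6.1.7 and 9.3.2. Saying so avoids a clash, because Appendix II also lists Hb <6 g/dl as a severe sign.

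In the three visit descriptions in 6.1.4, add a cross-reference to this rule.

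No new visit, form or measurement is needed. Gestation is already assessed at enrolment (by ultrasound, or by menstrual history and palpation where ultrasound is unavailable) and can be carried forward to the date of the episode. Clinical assessment and haemoglobin are already part of the work-up. The cost is a short wording amendment, which section 14.2 requires to be approved before use.

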## Enrolment

Upon presentation at first ANC visit, the PNGIMR study team will determine eligibility of participants (see 5.1 above for criteria) and administer written informed consent (see 14.3 for details of consent procedures).

Upon consent the baseline health assessment will be conducted and women will be assessed for the following exclusion criteria:

- chronic illness,
- symptomatic severe anaemia (Hb < 6 g/dl with symptoms such as breathlessness, weakness, dizziness), or
- permanent disability, that prevents or impedes study participation

Any one or more of the above criteria is sufficient to exclude women from study participation:

Women with severe anaemia and no, or minimal, symptoms, can be enrolled but will be treated according to local guidelines with a full course of antimalarial (SP+CQ, or SP + AZ, depending on randomisation group) and iron replacement treatment.

In the event an eligible woman is excluded from the study, the PNGIMR field study team will record the reason for exclusion in the study log book. Women diagnosed with symptomatic severe anaemia will be referred to Modilon hospital for treatment.

Enrolment and 1st treatment will be done at the same time, provided the woman is >13 weeks’ gestation.

Details of the procedures of Enrolment & 1st treatment Visit are given under 6.1 above.

Community controls will be enrolled in their villages by IMR staff, following village tok saves. Villages will be selected based on enrolment of pregnant women from these villages.

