## Treatment & Follow-up Visits

**7.3.1 Treatment Visits**

Following enrolment and 1st treatment women will receive further IPTp treatments at two intervals, at least 4 weeks after the previous administration. For details of procedure see 6.1.4 b & c.

At every ANC visit, only women who spontaneously report illness to study or ANC staff will be assessed on the spot for presence of malaria infections or anaemia.

Women found to have symptomatic severe anaemia (Hb < 6 g/dl) or other severe illness will be referred to the health centre for appropriate treatment. They will not be suspended from participation in the study but will be monitored again for anaemia and clinical status at their next ANC visit. Should their condition not have resolved by that time, they will be considered chronically ill and excluded from further participation in the study.

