### Procedures to be followed in the Event of Abnormal Laboratory Test Values or Abnormal Clinical Findings

If a participant is found to have symptomatic severe anaemia (Hb < 6 g/dl with anaemia symptomatology) she will be referred to Modilon Hospital for treatment.

The study coordinator will report such cases as SAE to the PI who will inform the DSMB and MiP SWG.

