### Type and Duration of the Follow-up of Subjects after Adverse Events

Management of adverse events will be according to best available practice. The study team will provide referral and transport to Madang (Modilon) Hospital where investigation and treatment will be provided through Government facilities.

All SAEs will be followed until satisfactory resolution or until the Principal Investigator or Study Clinician deems the event to be chronic or the patient to be stable.

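### After enrolment, symptomatic Hb <6 g/dl is sent to the health centre by section 7.3.1 but to Modilon Hospital, with an SAE report, by section 9.3.2

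*Combined protocol and SAP*

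**What the plan says.** Section 7.3.1 (Treatment Visits) covers women found at antenatal visits after enrolment to have symptomatic severe anaemia, Hb <6 g/dl. Such a woman "will be referred to the health centre for appropriate treatment". She stays in the study, and women in this position are to be "monitored again for anaemia and clinical status at their next ANC visit". If the condition has not resolved by then, the woman is classed as chronically ill and leaves the trial. No SAE step is given.

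Section 9.3.2 covers any participant found to have Hb <6 g/dl with symptoms of anaemia, whatever the route of detection. It says "she will be referred to Modilon Hospital for treatment" and adds: "The study coordinator will report such cases as SAE to the PI". The PI then informs the DSMB and the Malaria in Pregnancy safety working group.

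Section 6.1.7 (Passive Surveillance, Diagnosis & Treatment) deals with any Hb <6.0 g/dl found there: "study staff will treat the woman according to PNG national guidelines with a full course of antimalarials", together with albendazole and iron infusion. It does not mention symptoms of anaemia, onward referral or an SAE report.

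Other relevant text:
- Section 7.1 (Enrolment): "Women diagnosed with symptomatic severe anaemia will be referred to Modilon hospital for treatment". It describes the symptoms as Hb <6 g/dl "with symptoms such as breathlessness, weakness, dizziness".
- Section 5.2 also sends women excluded on health grounds to Modilon Hospital, and it lets women with Hb <6 g/dl but no significant symptoms enrol.
- Section 9.3.3, on managing adverse events: "The study team will provide referral and transport to Madang (Modilon) Hospital".
- The Study Design section brings women presenting with symptomatic anaemia into passive case detection.

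**The concern.** A nurse at a treatment visit works from the treatment-visit section. If she follows 7.3.1 as written, a woman with symptomatic Hb <6 g/dl goes to the health centre and is next looked at by the study at her following antenatal visit. Nothing in that section prompts hospital referral or an SAE form. Section 9.3.2 requires both for the same woman.

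Two things are at stake. The first is her care: section 6.1.7 places tertiary referral at the provincial hospital, so the two destinations are different levels of care. The second is safety reporting. Section 9.3.1 gives the site 72 hours to report a non-fatal SAE and the PIs 48 hours to notify the DSMB, and those limits are useful only if the event is recognised as an SAE. Section 9.4 sets no predefined halting rules, so DSMB oversight depends on the reports it receives. The synopsis includes safety in the primary objective, although the Objectives section states that objective in terms of low birth weight only and lists adverse events as a secondary outcome.

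**Working it through.** No arithmetic applies, and the plan states no figure to reproduce. The check is to compare trigger, destination and reporting duty, and then to look for text that reconciles them.

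| Section | Trigger | Destination of care | SAE report |
|---|---|---|---|
| 7.3.1 Treatment Visits | Symptomatic, Hb <6 g/dl, after enrolment | Health centre | Not mentioned |
| 9.3.2 Abnormal findings | Symptomatic, Hb <6 g/dl, any participant | Modilon Hospital | Required |
| 6.1.7 Diagnosis & Treatment | Any Hb <6.0 g/dl in passive surveillance | Not stated; study staff treat | Not mentioned |

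**7.3.1 against 9.3.2.** The trigger is the same and the destinations differ, so this is a direct conflict. On the SAE report, 7.3.1 is silent rather than contradictory. Neither section refers to the other, and no section says which prevails. I take Modilon Hospital to be the provincial hospital named in 6.1.7; section 9.3.3 treats the Madang hospital and Modilon as one.

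**Which destination is intended.** Sections 5.2 and 7.1 send such women to Modilon Hospital at enrolment, and 9.3.3 promises referral and transport there for adverse events. With 9.3.2, that makes four sections naming the hospital. Section 6.1.4 is looser: it sends women excluded at screening to the nearest facility. It concerns women who never enter the trial, so it does not alter the reading for participants.

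**6.1.7 against 9.3.2.** The trigger in 6.1.7 is wider and the text is about what is given, not where care ends. Symptomatic women fall within it, because passive case detection expressly includes symptomatic anaemia. The text can be read as first treatment before transfer, but it does not say so. This is a missing pointer, not a conflict.

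**A further group under 6.1.7.** Haemoglobin is measured there in women with presumptive malaria. Appendix II defines severe malaria as fever or recent febrile history, parasites on the slide, and any one of three signs, of which Hb <6 g/dl is one. A woman can therefore meet that definition without symptoms of anaemia. A rule for 6.1.7 based only on anaemia symptoms would miss her.

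**The case against.** The strongest reply is that 9.3.2 governs. It applies to any participant, it sits in the safety chapter where SAE duties belong, and a visit section need not repeat it. It also places the SAE report on the study coordinator, who, personally or through a designee, checks all forms on receipt (sections 13 and 15.1). There are other routes to an SAE report. Section 9.1 grades any event judged serious or life-threatening as grade 4, and 9.3.1 requires an SAE form for grade 4. Section 9.2 lists life-threatening events and allows medical judgement for intensive out-patient management. Health centres outside town have in-patient facilities, so admission there could meet the hospitalisation criterion. Section 9.3.1 has study physicians inform the PIs immediately. The re-check in 7.3.1 can also be read as concerning continued participation, not the course of treatment.

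Much of this stands on reporting: the silence of 7.3.1 and 6.1.7 does not mean that SAEs will be missed. These are partial backstops, however. The form checks are not described as SAE screens, and the other routes depend on admission or on judgement, whereas 9.3.2 makes the report automatic. None of this removes the difference in destination between 7.3.1 and 9.3.2.

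A reader might also infer that 6.1.7 contradicts 9.3.2, giving three competing instructions. The documents do not support that. Section 6.1.7 specifies treatment under national guidelines, which are not reproduced in the documents. It does not bar onward referral, and it places one of the study clinics in the hospital itself.

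**Conclusion.** The point holds as an internal inconsistency in a safety instruction. Sections 7.3.1 and 9.3.2 share a trigger and name different destinations; one of the two names Modilon Hospital and the SAE report, and the other names neither. Section 6.1.7 is a lesser gap: it lacks a symptom split and a cross-reference.

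The conclusion rests on reading the enrolment sections and 9.3.3 as showing that the hospital is the intended destination. It also assumes that no unseen standard operating procedure already reconciles the text; the documents refer to such procedures but do not include them.

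The size cannot be put as a number of women. Section 2.1 (Background Information) gives 13% with Hb <7 g/dl, but no share below 6 g/dl or with symptoms. A reader might infer under-counted SAEs in one arm or an effect on the primary outcome. The instructions do not depend on allocation and nothing in the documents links them to birth weight, so neither is claimed. The correction should be made for the women's care and for consistent SAE capture; the efficacy analysis is not in question.

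**What to change.** 1. In 7.3.1, state that a woman with symptomatic Hb <6 g/dl is referred to Modilon Hospital, with the transport promised in 9.3.3, and is reported as an SAE under 9.3.2. The re-check at the next antenatal visit can stay as a follow-up step.
2. In 6.1.7, keep treatment by study staff and describe it as first treatment. Add a cross-reference: women with symptomatic Hb <6 g/dl (symptoms as listed in 7.1), or who meet the Appendix II definition of severe malaria, are referred to Modilon Hospital and reported as SAEs. This is better than restricting treatment to women without anaemia symptoms, which would leave some severe malaria cases without a referral instruction.
3. Send a note to the sites with the amended wording.

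No extra participants, study visits or samples are needed. The downside is somewhat more referrals and SAE forms, since breathlessness, weakness and dizziness are non-specific in women who present ill. The documents give no basis for estimating how many more.
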